### **3.4.3 Stroop color word test**

The SCWT consisted of two sessions: word recognition (WR); color recognition (CR), and used software Eprime 2.0 Professional (Psychology SoftwareTools, Inc., Pittsburgh, PA), which allows online recording and voice-key triggering of the participants' verbal responses, for presenting the stimuli and collecting the data.

In order to further reduce the non-specific interfering factors of the Stroop task, such as practice times, stimulus encoding, contextual factors, color name facility, operational tasks, the amount of SOA, the subject's age and mood, the proportion of words and non-words (Rezaei, M., 2019; Edwards, S. et al., 1996), The stimuli were four-color word names presented in Chinese word as 红(RED), 黄(YELLOW), 蓝(BLUE) and 绿(GREEN). SCWT will produce two types of situations. In the case of the same word color, the meaning of the word matches the color ink. For example, the word BLUE is presented in blue ink; when the word color is inconsistent, the meaning of the word conflicts with the color of the ink. , Such as the word BLUE in red ink (Zhu, 2020). Participants will be asked to choose any a key (f, j, r, u) based on the word presented in four colors: red, yellow, blue, or green. The four colors used the left index finger, the right index finger, the left middle finger, and the right middle finger, respectively. For example, if the word color is yellow, whatever the word, the correct response is to press the "j" key with the right index finger. The stimulus consisted of randomly matched colors and words (120 incongruent trials, 40 congruent trials). All stimuli were presented for 500 ms followed by fixation point (+) for 250ms and a

stimulus remained displayed on the screen for a maximal duration of 1000 ms, see figure 4. The conflict effect of the two groups before and after inhibitory control training was evaluated through response time and error rate in both the congruent and incongruent stimulus (Xu et al., 2021). All subjects are required to practice until the correct rate is higher than 60% before the formal test can be conducted.

[figure not shown]

**Figure 4** SCWT process

#### 3.4.4 HRV measurement

In HRV measurement, uBioMacpa v70 (BioSense Creative, Korea) analyzes heart pulses by measuring pulse waves noninvasively on fingertip capillaries. It can check the vascular age and the degree of stress in the human body, and also can check whether the autonomic nervous system is abnormal. For example, uBioMacpa was used to measure autonomic stress levels.

The vascular health will be measured by deducing the vascular age from the age of the patient. Considering that there can be a difference in the measurement results, the heart rate variability of the autonomic nervous system will be measured 2.5 minutes when the subject is sitting down in quiet, see figure 5. The high-frequency values (HF), low-frequency values (LF), low-frequency ratio, mean heart rate per minute values (Mean BMP), standard deviation between pulses (SDNN), and the root mean square values of the standard deviation of pulses will be collected from HRV indicators. A pulse is a wave that produces when the blood which is pumped from the heart touches the blood vessel wall, which is repeated by the

heartbeat due to the changes of the blood flow. It is measured through the signal detected by applying light of a specific wavelength to the human body. The uBioMacpa stress measurement is based on the standards provided by the analysis of the average pulse variability signals from the North American Heart Rate Electrophysiology Society and the European Heart Association (Vanderlei et al., 2009).

[figure not shown]

**Figure 5** HRV measurement process

### 3.4.5 Physical Fitness test

The test indexes, procedures and sequence are as follows:

(1) Height and weight. Using Height and Weight scale (Weight scale, Jiangsu Suhong Medical Equipment Co., Ltd., China), it reflects the human development and nutritional status and the level of longitudinal growth of human bone marrow. During the Height test, the participant will stand on the floor of the height meter with bare feet and standing upright (the torso is straight, the upper limbs droop naturally, the heels are close together, the toes are separated by about 60°C, and the sacrum, heel, and both shoulder blades are in contact with the height meter column, The head is straight, the eyes are looking straight ahead, the upper edge of the tragus and the lowest point of the lower edge of the orbit are level. The record is in centimeters, with one decimal place. Use a height meter to test, the accuracy is 0.1cm. During the weight test, the participant naturally stood in the center of the scale and read the data after standing firm. Record the kilogram as a unit, and keep 1 decimal place. Using a weight scale test, the accuracy is 0.1kg. In addition, during the

test, the participants should reduce their clothing as much as possible; when getting on and off the scales, they should act lightly.

(2)Cardiopulmonary function. Using JH-1662 Electronic Spirometer, it reflects the volume and expansion capacity of human lungs. The accuracy of the JH-1662 Electronic Spirometer is 1ml, the accuracy of the flip spirometer is 20ml, and the accuracy of the barrel spirometer is 50ml. During the test, the participants inhale deeply until they can no longer inhale, and then point their mouths to the mouth of the spirometer and exhale deeply until they are exhausted. Test twice and take the maximum value. Records are in milliliters, rounded up. In addition, do not exhale too hard to prevent leakage; do not inhale twice; the mouth and mouth of the spirometer should be strictly disinfected.

(3)Muscle strength. JH-1881 Electronic Grip is used to test the grip strength, which reflects that the muscle strength of the human forearm and hand is a common functional indicator for evaluating the level of human growth and physical fitness. During the test, the participant turns the grip distance adjustment knob of the grip meter to adjust the grip distance to the appropriate grip distance, and then hold the grip meter firmly. Based on previous literature (Konharn et al., 2018), it is recommended that males should take a 1-minute standing rest posture when measuring grip strength, and young adult women should take a 1-minute sitting rest posture. Grip the handles with maximum force. Test twice and take the maximum value. The record is in kilograms, with one decimal place. In addition, it is forbidden to swing arms, squat, or touch the dynamometer to the body when exerting force: if the participant cannot distinguish a strong hand, test both hands twice.

(4)Flexibility. The mechanical flexionr is used for the sitting body flexion test, which reflects the flexibility of the human body. During the test, the participant sits on the mat, with legs straight, heels together, toes separated naturally, and the soles of the feet are pushed on the tester plate; then the palms are down, the arms are stretched flat, the upper body is bent forward, and the middle fingers of both hands are used. Push your fingertips to move forward until you can't push it. Test twice and take the maximum value. Records are in centimeters, with one decimal place. In Version number2.0 ; Dated 15thFeb. 2022

addition, before the test, the participant should do preparatory activities to prevent muscle strain. During the test, the knee joint must not be flexed, and there must be no sudden forward vibration. The positive and negative signs should be correctly filled in when recording.

(5)Balance. Using a one-leg standing test with eyes closed, it reflects the body's ability to balance. During the test, the participant stands naturally, and when he hears the "start" command, he lifts any foot while the tester starts the watch to time the test. When the tester's supporting foot moves or lifts the foot, the tester stops the watch. Take the test twice to get good results. The record is in seconds, with two decimal places. When testing, protect the surrounding area of the tester. The reliability of the SLS test is reported to be 0.89 and 0.86 when eyes are open and closed, respectively (Birmingham, 2000), and the Dynamic One Leg Stance was a fairly valid and reliable balance test for from 19 to 61 years participants with vision loss, acquired and experimental (Blomqvist & Rehn,, 2007).

(6) Power of lower limbs. Use a simple long jump mat for standing long jump test, which reflects the strength of the lower limbs of the human body. During the test, the participant stands with his feet naturally separated behind the jumper, and both feet simultaneously take off forward at the same time. The vertical distance between the heel and the jumper will be used as the test score. Each person jumped three times. Take centimeters as the unit, keep one whole number after the decimal point, and take the best score among the three test scores as the final score. In addition, before the test, the participant should do the necessary warm-up and stretching activities, and wait in an orderly manner at the test point. In the test, the participant has a stepping action when taking off, stepping on the line, crossing the line, the take-off score is invalid.

### **3.4.6 Body composition**

Body composition will be measured by body scale (Huawei Smart Scale 3 Pro, Huawei, China), and it has a professional eight-electrode and high and low frequency dual-frequency technology to comprehensively measure fluid data inside  
Version number2.0 ; Dated 15thFeb. 2022

and outside the cell. The principle is based on the HUAWEI TruFit™ human body composition model, which was developed by Huawei and the Hefei Institute of Material Science, Chinese Academy of Sciences. It uses bioelectrical impedance readings, large-scale data verification and artificial intelligence technology, and uses both low-frequency and high-frequency currents to calculate the results (Huawei, 2021). The accuracy of the results of this instrument is comparable to the professional gold standard and fat mass. The correlation between the skeletal muscles of the limbs and the DEXA professional human body analyzer can reach 0.94 (Laka, P., et al., 2021). The measurable range of weight is 2.5kg-150kg, which can provide accurate data of various body types from 6 to 80 years old. The indexes of body scale include: body water, body fat, protein level, muscle mass, bone mineral content (Huawei, 2021).

During the test, each subject will undergo a BIA performed using a Huawei body scale. All subjects will be measured in an assumed normally hydrated state and have not eaten or participated in physical activity a minimum of 90 mins prior to being measured. Huawei Smart Body Fat Scale 3 Pro adopts optical coating process, with ITO conductive coating and no explicit electrode. At the same time, Huawei Smart Body Fat Scale 3 Pro adopts an embedded handle design. Subjects only need to pull out the handle and touch the eight electrodes on the scale surface and handle respectively. With Huawei body composition detection algorithm, more accurate health data can be obtained. Before using it, you need to download the Huawei Sports Health App and pair it with a mobile phone running Android 6.0 or iOS 9.0 or above. Once paired, the subjects simply stepped barefoot on the scale, then pulled out the handle and clasped their hands for about 15 seconds to get a detailed report.

#### **3.4.7 rs-EEG measurement**

rs-EEG will be recorded by using the ActiCHamp amplifier with 64-channel active AgCl electrodes (actiCHamp Plus, Brain Products GmbH, Gilching, Germany), and it will be positioned on the scalp according to the modified 10–20 system.

Previous literature showed that Tai Chi can definitely increase alpha power  
Version number 2.0 ; Dated 15th Feb. 2022

during or after TC exercise (Li, X. et al., 2020; Nakatani, Y. et al., 2006), and maybe along with higher beta power and theta power (Liu, Y. et al., 2003; Wayne, P. M. et al., 2014). In order to measure these more accurately, Electrode gel will be inserted into the midfrontal (F3 & F4), central (C3 & C4), anterior temporal (T3 & T4), and parietal (P3 & P4) sites and referenced to the vertex (Cz) during recording (Field, T. et al., 2010). The horizontal electroophthalmogram will record a bipolar configuration between electrodes located on the lateral sides of each eye canthus; and vertical eye movements will be monitored by a bipolar montage located between electrodes above and below the right eye. Recording will be performed using an on-line 50Hz notch filter. After recording, the data will be restored to a rate of 500Hz and the total mean will be re-referenced (Barnett, K. J., 2008). It will apply both off-line filters with a high cut-off frequency of 0.1Hz and a low cut-off frequency of 35Hz. EEG preprocessing will be performed using BrainVisionAnalyzer software (BrainVisionAnalyzer, Brain Products GmbH, Gilching, Germany).

The whole process lasts eight minutes, EEG will be selected and recorded for three minutes (Gasser et al., 1996), see figure 6. Power spectrum will be computed during the HRV test. Spectral power analysis will be performed at four-second intervals by first applying the Welch window to the data and executing FFT. If the signal from three or more sites for that particular period exceeds  $100\mu\text{V}$ , the period will be rejected. The power spectrum will be averaged for each electrode and calculated for each band: alpha (8 -- 13Hz), beta (14.5 -- 30Hz), delta (0.5 -- 3.5Hz), and theta (4 -- 7.5Hz).

[figure not shown]

**Figure 6** rs-EEG measurement process

### **3.5 Exercise intervention and control procedures**

#### **3.5.1 Exercise intervention**

A review of previous meta-analysis shows that long-term exercise has a positive effect on cognitive function (Sibley & Etnier, 2003), evidence shows compared with 12 participants with general aerobic exercise, eight weeks of one-hour TC training, three times a week, had a stronger effect on brain plasticity (Cui et al., 2019). However, review literature shows that no effects on the MMSE were found following TC after 8 weeks, 24 weeks, or 24 months (Chang et al., 2014), and some findings suggest that TC had beneficial effects on cognitive function, but a longer duration was not associated with larger effects in older adults (Chen et al., 2021). Based on the primary results, looking at a previous RCT of aerobic exercise for cognition in (Lam, 2012; Hung et al., 2013; Xu, 2020 ), twelve weeks has also been suggested as a duration for interventions (Brown & Summerbell, 2009; Liu, 2018). Based on the above, the duration of this trial is determined to adopt a 12-week, 3 times a week, 45-minute RCT design.

TC exercise group received three weekly sessions of 24 Form TC group training for 12 weeks. Each training session consisted of 5 min of warm-up, 35 min of continuous sequential practice of learned forms, and 5 min of cool-down. Affected by epidemic control, two group training sessions will be held every week. The systematic approach will be taught by two instructors and can be viewed in Figure 7 (Zheng, et al., 2014), and another TC training session will be held in groups or completed by students themselves.

**Figure 7.** 24 Form Tai Chi

### **3.5.2 Exercise Intensity Monitoring**

Tai Chi had a lower metabolic demand and it is considered aerobic exercise at a low intensity. Lan, C. et al. showed the heart rate during TC practice was 58% of the heart rate reserve (Lan, C. et al., 2008) or 58% of the heart rate range (Lan, C. et al., 2001). In another study, the heart rate was also 56% of the age-predicted heart rate maximum, and Gong et al. reported that the HR in participants aged 48 to 80 was 104

bpm during the practice of simplified TC (Gong et al., 1981). The average heart rate of the TC group will be controlled at about 100 bpm during the 12-week exercise intervention. A bracelet will monitor the average heart rate of the TC group.

TC session instructor will be a physical educator with a Master's degree or above in sport science, and will have rich experience in TC teaching. The whole program will have two teaching assistants, and the student-teacher ratio across the program administration will be 15 to 1.

### **3.5.3 Control group**

The control group will be instructed to maintain their original daily routines and physical activity habits and to not receive any new or additional exercise interventions.

### **3.5.4 Safety evaluation**

Any adverse events, including any functional injury caused by the intervention, such as lumbar muscle strain, knee pain, and knee or ankle sprain, will be recorded on the case report form (CRF) during the intervention. If there is any adverse event, the investigator will respond accordingly based on the on-site situation. At the same time, adverse events will be reported to the ethics committee immediately to determine whether participants need to withdraw from the trial.

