## CHAPTER III

### Research Methodology

#### 3.1 Study design overview

The design of this study will be a RCT with two parallel groups with a 1:1 allocation ratio, allocation concealment and assessor blinding. The design follows the Consolidated Standards of Reporting Trials (CONSORT) and the Standard Protocol Items Recommendations for Interventional Trials (SPIRIT).

Eligible participants will be collected according to the requirements of the experimental design. According to the cluster sampling method, a two-arm, parallel controlled trial, randomized was conducted. The participants who will receive primary prevention education of cognition, mental health, and physical fitness will be divided into two groups: the 12-week 24 Form TC exercise intervention group (45 min per session, three sessions per week) or control group.

Cognitive performance, including executive function, memory, and processing speed, will be assessed by using SCWT at baseline prior intervention 2-3 days and within 2-3 days after the 12-week intervention. In addition, before and after the 12th TC training session, all participants in the TC exercise group will be only assessed cognitive performance by using SCWT and HRV test.

Furthermore, both the function and structure of brain regions related to cognitive performance will be measured by using rs-EEG, and autonomic nerves in the nervous system will be measured by using HRV, and fitness health factors (power of lower limbs, body mass index, body composition, cardiopulmonary function, muscle strength, balance, flexibility) will be measured at baseline prior intervention 2-3 day and within 2-3 days after the 12-week intervention. In addition, mental health will also be assessed by using Depression Status Inventory and State-Trait Anxiety Inventory Version at baseline prior intervention 2-3 days and within 2-3 days after the 12-week intervention.

All data collection of the group assignments will be blinded. The flow diagram

for this study is presented in figure 3.

[figure not shown]

**Figure 3** Flow diagram of the study design.

Version number2.0 ; Dated 15thFeb. 2022

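### The stated adverse-event recording window omits both fitness-test visits and is ambiguous for controls, so event counts would be incomplete and unequally ascertained between arms

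*Protocol*

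**What the plan says.** Section 3.5.4 (Safety evaluation) is the protocol's only provision on adverse events. Its scope is wide: "Any adverse events, including any functional injury caused by the intervention". Its recording rule carries a time limit: such events "will be recorded on the case report form (CRF) during the intervention". No first or last day is given. A further sentence has no time limit: "adverse events will be reported to the ethics committee immediately to determine whether participants need to withdraw from the trial".

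Section 3.1 times the fitness measures outside the 12 weeks: they "will be measured at baseline prior intervention 2-3 day and within 2-3 days after the 12-week intervention". Section 3.3.2 applies pre-test1 and post-test2, including the physical fitness tests, to both arms.

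Section 3.4.5 acknowledges that these tests can injure. For sit-and-reach, "before the test, the participant should do preparatory activities to prevent muscle strain". It also asks for protection around the person during the eyes-closed balance test, and for warm-up and stretching before the standing long jump.

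On contact with participants, section 3.5.1 gives the tai chi arm two taught group sessions a week, while "another TC training session will be held in groups or completed by students themselves". For the other arm, section 3.5.3 says: "The control group will be instructed to maintain their original daily routines and physical activity habits".

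**The concern.** A recording window that follows the intervention, when the physical testing is placed just before and just after it, leaves the test visits without a stated duty to record. The participants are self-reported sedentary students. They perform maximal grip, sit-and-reach, eyes-closed one-leg standing and three long jumps. The injuries that section 3.5.4 names (strain, knee pain, knee or ankle sprain) could plausibly arise from these tests too. A strain at pre-test1 that is not written down and comes to light in week 1 could later be taken for a tai chi injury.

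The second issue is comparability. A window worded around the intervention has no obvious meaning for people who receive none. One arm also meets staff every week, and the other has no stated contact between test visits. Raw event counts would then partly reflect who was asked. An analysis plan cannot repair this, because it cannot recover events that were never collected.

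**Working it through.** The point rests on comparing sections. The arithmetic only sizes the exposure.

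**1. The number enrolled (section 3.2.2).** The inputs are means 0.392 and 0.475, SDs 0.087 and 0.097, two-sided 5% and 80% power. With 2σ² taken as the sum of the two variances, n per group = (1.96 + 0.84)² × (0.087² + 0.097²) / 0.083² = 7.84 × 0.016978 / 0.006889 = 19.3, so 20. The stated 25 per group corresponds to 20 / (1 − 0.20). The plan's 20 and 25 therefore reproduce, the 20% dropout being implied and not stated.

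**2. Window against test visits.**

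| Item | Timing | Arms | Inside the literal window? |
|---|---|---|---|
| CRF recording (3.5.4) | during the intervention, weeks 1-12 | not stated | – |
| Pre-test1 battery (3.1, 3.3.2) | 2-3 days before | both | no |
| Tai chi sessions (3.5.1) | weeks 1-12 | tai chi | yes |
| Post-test2 battery (3.1, 3.3.2) | within 2-3 days after | both | no |

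Two of two batteries lie outside. Sittings without a prescribed CRF entry: 50 × 2 = 100. If only 20 per group return for post-test2, it is 50 + 40 = 90.

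**3. What might be lost.** The documents give no injury rate per sitting, so these rates are assumptions. With independent sittings, P(at least one test injury) = 1 − (1 − p)^m:

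| Assumed p | m = 100 | m = 90 |
|---|---|---|
| 0.5% | 39% | 36% |
| 1% | 63% | 60% |
| 2% | 87% | 84% |

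This shows only that at least one test injury is not far-fetched over a plausible range. It does not estimate harm.

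**4. Contact by arm between the test visits.** Tai chi: 2 × 12 = 24 taught group classes at minimum, plus the SCWT and HRV assessment around the 12th session. Up to 1 × 12 = 12 of 3 × 12 = 36 sessions (33%) may be self-practised. Controls: none stated. Section 1.2 mentions a fourth-week evaluation, but sections 3.1 and 3.3.2 confine it to the tai chi arm.

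Suppose both arms have the same true risk r, and a fraction s of events comes to notice. The expected counts are 25 × r × s(TC) and 25 × r × s(control), and their ratio is s(TC)/s(control) whatever r is. With regular contact in one arm only, s(TC) is likely the larger. The apparent excess under tai chi would then come from ascertainment. The protocol gives no values for s, so the size of this bias cannot be computed.

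**The case against.** The best reply is that the rest of section 3.5.4 is broader than the recording clause, and much of this reply stands.

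- **Controls.** A reader might infer that controls are excluded from recording. The text does not say so. The scope is any adverse event, with no arm limit, and section 3.1 uses the intervention as a calendar period around which measurements in both arms are timed. On that usage controls share the 12-week window. What remains is ambiguity plus unequal contact.
- **Test injuries.** A reader might infer that they would go uncounted altogether. The sentences on the investigator's response and on ethics-committee reporting carry no window, so a sprain at post-test2 should be acted on and reported. But the stated purpose of that report is the withdrawal decision, and no CRF record is prescribed for it. The CRF is not shown, so it cannot be said that it has no room for such events.
- **Attribution.** A reader might infer that only intervention-caused injuries are collected, or that unblinded staff make the attribution. Causation by the intervention is given as an example of what is included, and no section says who completes the adverse-event record.
- **Relative risk.** Nothing in the protocol ranks the tests as riskier than 36 exercise sessions. Screening, experienced testers and warm-up instructions all reduce the risk of the tests.
- **Purpose.** Safety is not among the aims in section 1.4 or the outcomes in section 3.6, and no between-arm safety test is planned. Even with perfect ascertainment, zero events in 25 leaves a one-sided 95% upper bound of 1 − 0.05^(1/25) = 11%. This limits how much the change can deliver. It does not justify a window that leaves out known hazards.
- **Self-practice.** Those sessions fall inside the window, 12 of 36 is a maximum, and injuries can be mentioned at the next class.

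**Conclusion.** The point holds in a limited form. Read literally, section 3.5.4 prescribes no CRF entry for either fitness battery in either arm (100 of 100 planned sittings with 50 enrolled and no dropout), although section 3.4.5 recognises hazards in those tests. For controls the window is ambiguous and no contact is stated between test visits. Ascertainment would therefore be unequal and a comparison of event counts unreliable.

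It would go too far to conclude that no between-arm comparison is possible. If the window is read as the common 12 weeks, events can be recorded and compared in both arms, with the ascertainment caveat. The number of events at stake is unknown, because the documents give no injury rate. The conclusion rests on a literal reading of the recording clause and on the absence of any other stated contact with controls. It touches no efficacy outcome. It is a low-cost improvement to safety recording.

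**What to change.** In section 3.5.4:

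- Replace the present time limit with: *from signed consent to completion of post-test2, in both arms, whatever the suspected cause*. Consent precedes baseline testing (section 3.2.2), so this covers both batteries.
- Record relation to tai chi, to testing, or to neither as a separate CRF field.
- Ask both arms the same short question about any new injury, pain or illness at the end of each test visit. Base any between-arm count on those answers.
- At the next group class, ask tai chi participants about injuries in self-practised sessions. Keep those reports apart from the between-arm count, since controls have no equivalent.

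A weekly message to both arms is optional. It would reduce reliance on recall at post-test2, but it adds contact for controls in a trial with depression and anxiety outcomes.

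The cost is amended wording and a small CRF addition, with no extra visits. The drawback is a longer list of minor, unrelated events. Without interim contact, control events within the 12 weeks still depend on recall, and anything that appears after post-test2 closes stays outside the record.
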